### Criteria for discontinuing or modifying allocated interventions {11b}

Study participation will be discontinued if a patient withdraws their written informed consent. In case of a serious adverse event (SAE), we will investigate a causal link between intervention and the occurrence of SAE and evaluate whether trial continuation would be a risk to the client, and whether modifications should be made to the intervention (e.g. support sessions). SAEs are defined as events that (1) result in death, (2) are life-threatening, (3) require hospitalisation or cause prolongation of existing hospitalisation, (4) result in persistent or significant disability or incapability, (5) are a congenital anomaly or birth defect or (6) require intervention to prevent permanent impairment or damage (such as acute suicidality). All SAEs that are reported by the patients will be evaluated by the clinical psychologist on site and the PI. Whenever a patient is withdrawn from the trial, the reasons for the withdrawal or treatment discontinuation together with the corresponding dates will be recorded. If a patient completely drops out from the study, a final examination will be conducted if possible. In particular, every effort will be taken to assess the primary outcome at follow-up. If a patient does not return for a scheduled visit, every effort will be made to contact the person to arrange further visits according to the protocol. Depending on the number of dropouts, missing values in primary outcome may either be excluded from the analysis or replaced according to the intention-to-treat principle or multiple imputation methods, respectively.

We expect that our sample of patients living in districts with high levels of urban violence may experience new traumatic events or death of family members, relatives or friends during the period of treatment. Patients will remain in the trial, but exposure sessions may be paused for few weeks. Support sessions may be provided according to the patient’s needs.

### Strategies to improve adherence to interventions {11c}

Adherence to the NET manual will be ensured through the narrations produced in NET and close supervision by a NET expert (2 h per week) recording the outcome for the according sessions.

### Relevant concomitant care permitted or prohibited during the trial {11d}

In both arms, patients are permitted to continue psychopharmacological medication as prescribed by their psychiatrist (unless prescribed neuroleptics indicating acute psychotic symptoms).

### Provisions for post-trial care {30}

If one of the conditions is more effective, patients who are still need (fulfilling the diagnostic criteria for PTSD) will be offered the according treatment.

### Outcomes {12}

Outcomes will be measured 3 and 6 months after the treatment. PTSD symptoms will be assessed as primary outcome using the PTSD Symptom Scale Interview for DSM-5 [24]. The Patient Health Questionnaire [25] will be used to measure depression severity. To assess trauma-related dissociation, we will use the Shutdown Dissociation Scale [26]. Substance involvement will be evaluation with the Alcohol, Smoking and Substance Involvement Screening Test [27]. Functionality will be assessed with the Work and Social Adjustment Scale [28]. Ongoing violence will be assessed by the scale Things I’ve seen and heard [29] and three questions asking whether the client has experienced any threat to physical or social integrity or was actively involved in violent perpetration.

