#### Narrative Exposure Therapy

NET will be delivered in 8–12 individual sessions of 90–120 min each in length by Brazilian NET therapists. The flexible number of sessions allows to test NET under naturalistic conditions and to adapt to the client’s trauma history. The initial session involves the construction of a lifeline whereby traumatic events are mapped out in chronological order and situated in the context of the patients’ lifetime period, as well as the wider systemic, and socio-political context at the time. A therapy plan is constructed according to the idiosyncratic experiences of the individual and traumatic events. In the subsequent exposure sessions, the most traumatic experiences are re-lived (emotional, sensory, cognitive, interoceptive) in order to transform the fragmented report of traumatic events into a coherent narrative. The therapist makes a written record of the event, and at the beginning of the next session, the narration is read to the patient and corrected for potential discrepancies. In the last session, the participant receives a written report of his/her biography.

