### Participant timeline {13}

An appointment for baseline assessment of trauma-related psychopathology will be scheduled by our study focal point with consenting individuals. Trained psychological interviewers will administer a structured, paper-based clinical interview (baseline, T0) to determine eligibility. Eligible patients will then be randomised and those allocated to the experimental condition will be contacted to start treatment at the next possible time point. Patients in the control condition will continue to benefit from the services of public health centres. Three and 6 months later, follow-up interviews (T1 and T2) will be conducted with the participants.

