
### Plans to promote participant retention and complete follow-up {18b}

Follow-up data will be collected 3 and 6 months after treatment delivery. Patients who discontinued the trial will be provided care in the health centre.

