## Trial status

Interviewer and NET trainings have been provided successfully. Recruitment of patients, treatment delivery, and supervision are ongoing.

Protocol version 1.1 (last major updates September 29, 2019; last minor revisions February 4, 2020, and January 16, 2021 (plus amendment to the protocol)

Recruitment of the first patient: October 17, 2019

Last day of recruitment (expected): March 30, 2020, postponed to January 31, 2021

Last follow-up (expected): September 30, 2020, postponed to February 30, 2022

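### The T1 and T2 visits have no consistent starting point, and the post-treatment rule cannot date a visit in the TAU arm, so the arms could be compared at different times since randomisation

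*Protocol article*

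**What the plan says.** Three sections of the protocol article set the timing of the follow-up interviews, which carry the primary PTSD outcome.

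- Outcomes {12}: "Outcomes will be measured 3 and 6 months after the treatment".
- Plans to promote participant retention and complete follow-up {18b}: "Follow-up data will be collected 3 and 6 months after treatment delivery".
- Participant timeline {13}: after the baseline interview, randomisation, the contact to begin NET and the continuation of health-centre care for controls, "Three and 6 months later, follow-up interviews (T1 and T2) will be conducted with the participants".

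The length of the NET course varies between patients. Participant timeline {13} says that "those allocated to the experimental condition will be contacted to start treatment at the next possible time point". The Narrative Exposure Therapy section says "NET will be delivered in 8–12 individual sessions of 90–120 min each in length by Brazilian NET therapists", without giving the spacing of sessions. Section {11b}, on new traumatic events during treatment, adds: "Patients will remain in the trial, but exposure sessions may be paused for few weeks".

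The Treatment as usual section describes care that may already be running at randomisation, is not standardised, and has its dose assessed retrospectively at follow-up. No number of contacts, duration, end or reference date is given for it.

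The analysis in Statistical methods {20a} treats time as three nominal occasions: baseline, month 3 and month 6.

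**The concern.** The timing of the primary outcome is a core design item, and here it is stated in two ways that do not match. Two sections count from treatment. The third gives a sequence in which the only available starting points are randomisation or the start of care.

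The post-treatment rule also fails in one arm. Care that has no end cannot be followed by an interview 3 months after its end. Someone has to supply a starting date for TAU patients, and the article does not say which.

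Randomisation protects the NET versus TAU comparison only when both arms are measured at comparable times. PTSD severity can change with time since randomisation, through natural recovery, further exposure to violence, or both. If staff counted NET patients from their last session and TAU patients from randomisation, the arm difference would include a difference in elapsed time. The model would label both sets of interviews month 3 and month 6, and nothing in the output would show it.

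**Working it through.** **1. The dates under Trial status.** These are the only figures in the article that bear on the clock. The sample-size figures do not enter. One month is 365.25 / 12 / 7 = 4.35 weeks, so 3 months is 13.0 weeks and 6 months is 26.1 weeks.

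- First set of dates: 30 March 2020 (last recruitment) to 30 September 2020 (last follow-up) is 184 days, or 26.3 weeks. Subtracting 26.1 weeks leaves 0.2 weeks for the NET course of the last recruit. That fits a clock running from recruitment and not one running from the end of NET.
- Postponed dates: the line reads "Last follow-up (expected): September 30, 2020, postponed to February 30, 2022", and its second date does not exist. Taking 28 February 2022 instead, the gap from 31 January 2021 is 393 days, or 56.1 weeks. Subtracting 26.1 weeks leaves 30.0 weeks for NET, which is compatible with a post-treatment clock.

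The first dates have been replaced, so they only hint at the original intention. They do not settle which clock is in force.

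**2. Lag if the arms use different anchors.** Suppose NET is counted from the end of treatment and TAU from randomisation.

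- Lag (weeks) = wait before NET + sessions × weeks between sessions + pause.
- NET T1 = lag + 13.0. NET T2 = lag + 26.1. TAU T1 and T2 are at 13.0 and 26.1.

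The 8 to 12 sessions come from the article. The spacing (weekly or fortnightly), the wait (0 to 4 weeks) and the pause (0 to 4 weeks) are assumptions, because the article gives no figures for them.

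| Spacing | Sessions | Wait + pause (weeks) | Lag (weeks) | NET T1 (week) | NET T2 (week) |
|---|---|---|---|---|---|
| Weekly | 8 | 0 | 8 | 21.0 | 34.1 |
| Weekly | 12 | 0 | 12 | 25.0 | 38.1 |
| Weekly | 12 | 4 + 4 | 20 | 33.0 | 46.1 |
| Fortnightly | 8 | 0 | 16 | 29.0 | 42.1 |
| Fortnightly | 12 | 0 | 24 | 37.0 | 50.1 |
| Fortnightly | 12 | 4 + 4 | 32 | 45.0 | 58.1 |

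With weekly sessions and a lag of 8 weeks or more, the NET T1 interview is nearer in time to the TAU T2 interview (week 26.1) than to the TAU T1 interview (week 13.0).

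**3. Lag if both arms are counted from randomisation.** T1 is at week 13.0 and T2 at week 26.1 in both arms, so the lag is 0. What changes is how much NET has been delivered by T1. With weekly sessions and no delay, NET ends in weeks 8 to 12, which is 1 to 5 weeks before T1. With 12 weekly sessions and a 4-week wait it ends in week 16, 3 weeks after T1. With fortnightly sessions it ends in week 16 at the earliest, also after T1.

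**The case against.** The strongest reply is that the two explicit statements agree with each other, and that the timeline is a loose narrative whose word for the interval has no stated anchor. The article is also condensed, and a matched TAU reference date is the kind of operational detail a full protocol may hold. Part of this stands: the timeline does not say that it counts from enrolment, and the absence of a TAU date here does not show that timing was unequal. But the article does not merely omit a detail. It states a rule for the primary outcome that has no meaning in one arm, next to a second description that does not match it.

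Four stronger readings are tempting, and the documents do not support them.

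- A reader might infer that NET patients will be interviewed later than TAU patients. No section starts the TAU clock at randomisation. The text allows that mismatch without prescribing it.
- A reader might infer that the comparison is confounded with time whichever clock is used. On a common randomisation clock the elapsed time is equal. An interview during NET affects how much treatment the T1 contrast captures, which is a different matter.
- A reader might want a bias in scale points. That needs a monthly drift in symptom score, which the article does not give. Even the sign is open: recovery over time would favour the arm assessed later, and new trauma, which section {11b} expects, would disfavour it.
- A reader might take the first Trial status dates as proof of an enrolment clock. They are superseded, and the date that does not exist is a clerical slip with no bearing on comparability.

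The primary model also enters community and intimate partner violence scores as fixed terms. That bears on differences in exposure to violence, but it does not remove a difference in elapsed time.

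**Conclusion.** The point holds as an inconsistent visit anchor for the primary outcome, together with a post-treatment rule that cannot be applied to TAU. The possible consequence is a lag between arms of 8 to 12 weeks at each visit if NET is counted from treatment end and TAU from randomisation, assuming weekly sessions, no wait and no pause. The lag reaches 20 weeks with a 4-week wait and a 4-week pause, and is longer still with wider session spacing. Whether any lag occurs depends on how staff date TAU interviews, which the article does not say. The direction of any resulting bias is unknown and its size in score points cannot be derived. Nominal visit labels in the model would hide it.

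**What to change.** Reconcile Outcomes {12}, Participant timeline {13} and the retention section {18b} on one anchor that works in both arms. This can be time from randomisation, or a TAU reference date matched to the NET schedule. Give both arms the same visit windows. If randomisation is chosen, state that T1 may fall before NET is complete for some patients, so that the T1 contrast is read accordingly. Correct the impossible date under Trial status.

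For all patients, including those already followed up, tabulate months from randomisation to each interview by arm. Prespecify a sensitivity analysis of the primary model that uses this actual time in place of the nominal visit.

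The cost is a protocol clarification, some rescheduling of remaining interviews and one extra analysis. There are two limits. Recruitment was expected to end on 31 January 2021, so changing the anchor only for remaining interviews would mix two schedules within the trial. The tabulation should therefore show which schedule each interview followed. And if interview times barely overlap between arms, adjusting for actual time relies on an assumed symptom trajectory and should be reported with that caveat.

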### Participant timeline {13}

An appointment for baseline assessment of trauma-related psychopathology will be scheduled by our study focal point with consenting individuals. Trained psychological interviewers will administer a structured, paper-based clinical interview (baseline, T0) to determine eligibility. Eligible patients will then be randomised and those allocated to the experimental condition will be contacted to start treatment at the next possible time point. Patients in the control condition will continue to benefit from the services of public health centres. Three and 6 months later, follow-up interviews (T1 and T2) will be conducted with the participants.

### Sample size {14}

Following similar studies in regions with ongoing violence, sample size per group was calculated based on a medium to high within-group Cohen’s *d* effect size for our primary outcome measure PTSD [18, 19, 30] with a power of >.70 and a significance level of .05, a sample size of 25 per group was suggested. However, to allow for a more robust analysis testing for a smaller effect due to the ongoing violence and in regard to covariates (level of ongoing violence) and secondary measures (depression, dissociation, substance involvement and medication, functioning), we will aim at a sample size of 30 per group.

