### Objectives {7}

The aim of the study is to test the effectiveness of NET in a setting on ongoing violence in comparison to a treatment as usual (TAU) control group.

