### Trial design {8}

The present study is a two-arm parallel group, observer-blinded, randomised, actively controlled clinical superiority trial with an allocation ratio of 1:1.

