## Statistical methods

### Statistical methods for primary and secondary outcomes {20a}

To test the efficacy of NET in comparison to TAU in regard to primary (PTSD) and secondary (depression, shutdown dissociation, substance involvement, functionality) outcomes, we plan to use separate generalised linear mixed models (GLMMs) in R (R Core Team, 2018). To investigate the influence of ongoing violence, we will enter the sum scores for community and intimate partner violence as fixed model terms. To account for non-independence of measurements, we will include individuals as random model terms. To account for repeated measures, we will control the within-group variance for the effect of time, i.e. baseline and 3- and 6-month follow-ups, according to Field et al. [41]. To estimate the significance of the fixed terms, we plan to fit the models using maximum likelihood (ML) and compare models with and without each fixed term using likelihood-ratio tests (LRTs) [42]. In cases where interaction terms are significant, we will use post hoc Tukey tests using the R package emmeans [43] to assess which contrasts differ significantly. To correct for multiple comparisons controlling for the false discovery rate, we will adjust *P* values using the R built-in function p.adjust according to Benjamini and Hochberg [44]. Additionally, effect sizes will be estimated by calculating Cohen’s *d* [45] for within- and between-group differences. Clinically significant change will be calculated using the reliable change index, following Jacobson et al. [46] for clinical outcomes (PTSD, depression).

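### The sample size rests on a within-group effect, so the stated power above .70 does not describe the NET versus TAU comparison that the trial tests

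*Protocol article*

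**What the plan says.** All the figures are in Sample size {14} of the protocol article. The section says the "sample size per group was calculated based on a medium to high within-group" Cohen's d for PTSD, citing similar studies in regions of ongoing violence, and that "with a power of >.70 and a significance level of .05, a sample size of 25 per group was suggested". It gives no numerical d, no test and no sidedness.

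The target is then raised: "we will aim at a sample size of 30 per group". One reason is "to allow for a more robust analysis testing for a smaller effect due to the ongoing violence"; covariates and secondary measures are the others. No effect size or power is attached to this step.

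The hypothesis is between groups throughout the rest of the article. Objectives {7} sets out to test NET "in comparison to a treatment as usual (TAU) control group". Trial design {8} describes an "actively controlled clinical superiority trial with an allocation ratio of 1:1". Statistical methods {20a} uses mixed models over baseline, 3 and 6 months to compare NET with TAU on the primary and secondary outcomes. The section on treatment as usual lists medication, supportive listening, problem solving and social support, so the control arm receives active care.

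**The concern.** A within-group d measures the change in one arm from before to after treatment. It combines the specific effect of treatment with natural recovery, regression to the mean and the effect of being in care. Patients enter because they meet PTSD criteria at baseline, so some regression to the mean can be expected in both arms, and TAU may bring improvement of its own. The difference between NET and TAU is what remains once the shared part is removed. It can be well below the pre-post d in the NET arm, and a two-sample comparison also has a different variance from a paired one.

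The power sentence therefore answers a question that the trial does not ask. A reader who takes power above .70 as the power for NET against TAU could give a null result more weight than the design supports. This matters most if the effect is smaller under ongoing violence, which the section itself anticipates.

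**Working it through.** **Inputs from the protocol article.** Power above .70, alpha .05, 25 per group calculated, 30 per group targeted, 1:1 allocation, follow-up at 3 and 6 months.

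**Assumptions not in the article.** A medium-to-high d is taken as 0.5 to 0.8, tests are two-sided, and correlations between time points are 0.5 where used.

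**Formulae (noncentral t).** Power = P(|T| > t(0.975, df)) with noncentrality λ.
- Paired (within-group) test: λ = d√n, df = n − 1.
- Two-sample test, n per group: λ = d√(n/2), df = 2n − 2.

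**Step 1: can 25 per group be reproduced?** Not uniquely, because d, test and sidedness are missing. Solving for the d that gives 70% power at n = 25:
- Paired: d = 0.52 two-sided (0.45 one-sided).
- Two-sample: d = 0.72 two-sided (0.62 one-sided).

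Both two-sided values lie inside the assumed range. In the other direction, a paired two-sided test needs 27, 17 and 12 patients for 70% power at d = 0.5, 0.65 and 0.8. A two-sample test needs 51, 31 and 21 per group.

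**Step 2: how much does the choice of contrast matter at the same d?** At n = 25 and d = 0.5:
- Paired: λ = 0.5 × √25 = 2.50, power 67%.
- Two-sample: λ = 0.5 × √12.5 = 1.77, power 41%.

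At d = 0.8 the figures are 97% and 79%.

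**Step 3: unadjusted two-sample power at one time point.**

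| n per group | d = 0.5 | d = 0.65 | d = 0.8 | d for 70% power |
|---|---|---|---|---|
| 25 | 41% | 61% | 79% | 0.72 |
| 30 | 48% | 70% | 86% | 0.65 |
| 24 (30 × 0.8, an assumed 20% loss) | 40% | 60% | 77% | 0.73 |

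**Step 4: closer to the planned analysis, 30 per group.**
- Baseline adjustment, one follow-up, r = 0.5: the residual variance is 1 − 0.5² = 0.75, so d is divided by √0.75 = 0.866. Effects of 0.5 and 0.65 become 0.577 and 0.751. Power is 59% and 82%.
- Mean of both follow-ups with baseline adjustment, all correlations 0.5, constant effect: the variance of the mean is (1 + 0.5)/2 = 0.75 and its covariance with baseline is 0.5, so the residual variance is 0.75 − 0.25 = 0.50. Dividing by √0.50 = 0.707 gives 0.707 and 0.919. Power is about 77% and 94%.

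**Step 5: what if TAU patients improve too?** As an illustration, take a TAU pre-post d of 0.2 on the same SD. NET pre-post effects of 0.5 and 0.8 then leave between-group effects of 0.3 and 0.6. Unadjusted power is 18% and 55% with 25 per group, and 21% and 63% with 30.

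**The case against.** A reader might infer that a one-sample pre-post test was used and that the trial lacks the power it claims. The article supports neither. It names no test, and 25 per group also follows from a two-sample calculation at d = 0.72. If that was the route, the test and variance were right and only the source of d is in question. At a true between-group d of about 0.72 or more, 25 per group reaches 70%, and the actual target of 30 reaches it at 0.65.

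The unadjusted t-test is also not the planned analysis. The mixed model uses baseline and both follow-ups, and at d = 0.5 with 30 per group the calculated power runs from 48% to about 77% depending on how much of that information is used. Quoting only the low end would be unfair, although a group-by-time test with several degrees of freedom would fall below the top figure. The 20% loss is an illustration: the article states no attrition rate, and its missing-data section keeps patients with partial data in the model.

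All of this stands and limits the point. It does not remove it. Whichever formula was used, the d put into it is described as within-group, and a better analysis does not turn a pre-post effect into a between-group one. The rise to 30 does not repair this, because no effect or power is attached to it.

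**Conclusion.** Wrong as written, and it should be fixed. The power claim has the wrong basis: an effect described as within-group is used to size a superiority comparison between arms, and no power for that comparison appears anywhere in the article. The mismatch itself rests on the article's own wording and needs no assumption.

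Its size does need assumptions. With 30 per group and two-sided .05, power for a between-group d of 0.5 is 48% unadjusted, 59% with baseline adjustment and about 77% with both follow-ups averaged. For d = 0.65 the figures are 70%, 82% and about 94%. The values of d, the sidedness, the correlations of 0.5 and the constant effect over time are all assumed. Whether the trial is underpowered cannot be settled from the article, since that depends on the true NET versus TAU difference.

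**What to change.** Leave N unchanged. In Sample size {14}, keep the account of how 25 and then 30 were chosen, since recruitment began in October 2019 and removing it would hide the actual basis. Add that this basis does not give the power for NET versus TAU. Then add a between-group statement, labelled as a later calculation, with sidedness, time point and assumptions. For example:

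- With 30 per group and a two-sided .05 test, an unadjusted comparison at one follow-up has 70% power at a between-group d of 0.65 and 48% at d = 0.5.
- With baseline adjustment at an assumed correlation of 0.5, power is 82% and 59%.
- With both follow-ups averaged, all correlations assumed to be 0.5 and a constant effect, power is about 94% and 77%.
- If 20% were lost (an assumption, 24 per group), the unadjusted figures would be 60% and 40%.

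The cost is one paragraph of text and a less favourable stated power for a medium effect. No patients, outcomes or procedures change.
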